#### Data collection

At each assessment point, questionnaires will either be posted to participants and returned via post, or participants will be provided with a link to a website where they can complete the measures online. Measures will be collected at baseline, post intervention (10 weeks post randomisation), 8 weeks post intervention (18 weeks post randomisation), and postnatal follow-up (34 weeks post randomisation); the measures of mother-child relationship, infant temperament and infant sleep will be collected at postnatal follow-up only. Partners will also complete measures of anxiety, mood and quality of couple relationship at each assessment point.

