### Study setting

Participants will be recruited through UK National Health Service (NHS) antenatal scanning clinics at their 12-week scan in London and the South West of England. The intervention will be delivered to participants in these locations as a part of antenatal services.

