### Recruitment procedure

After completing the screening questionnaire for anxiety (GAD-7; [38]) and a small number of demographic questions in the antenatal scanning clinic, women who meet eligibility criteria will be sent information on the full study and a consent form. A researcher will follow up with a phone call and, if the individual is willing to take part, will guide them through the consent form. The participant will be directed to send back the signed consent form via mail or online, after which the researcher will provide the participant with the option to complete the baseline questionnaires via mail or online. Upon completion and receipt of the baseline measures, participants will be randomised (see Fig. 1). Women’s partners who agree to participate in the study will be consented separately.

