### Randomisation

In phase 2, participants will be randomly allocated on a 1:1 basis to either the intervention group or the treatment as usual group using a sealed envelope method, managed by a staff member in a separate research group. Participants will be informed of their group allocation by a researcher over the telephone.

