### Sample size

In line with guidelines for pilot RCTs, no formal power calculation has been conducted [39]. A sample size of 30 participants per arm is recommended for feasibility studies as providing sufficient data to gain an accurate estimation of the feasibility and acceptability of the intervention and trial methods [40], and to provide a reasonable range of estimates of the sample size required for a definitive RCT [41]. Thus, 30 participants will receive the intervention (in four groups of approximately 7–8 participants each, plus participants’ partners where possible) and 30 will receive treatment as usual.

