### Intervention

The research will adapt and build on existing interventions utilising CBT principles. One such intervention, *Towards Parenthood*, is a workbook-based, psychoeducational intervention that focuses on making the transition into parenthood and on the emotional, social and psychological issues that can arise during pregnancy and early parenthood. The *Towards Parenthood* intervention aims to help expectant parents develop effective coping and parenting skills. In addition, it provides specific information about anxiety, stress and mood problems and incorporates fundamental elements of CBT, which addresses maladaptive cognitions and behaviours. In a clinical trial in Australia [28] it was shown to be effective in reducing symptoms of anxiety (*d* = 0.58), stress (*d* = 0.59) and depression (*d* = 0.6) in women at postnatal follow-up. The workbook incorporates nine sections and women in the Australian trial additionally received weekly telephone support from trained psychologists or postgraduate psychology trainees.

The planned intervention will be developed for optimal efficacy, feasibility and acceptability with a broad population of pregnant women experiencing a range of anxiety symptoms of differing severity, with the aim of reducing the overall population burden of antenatal anxiety.

The proposed format will be a manualised brief intervention, blended with group support. We plan to deliver three group sessions in the antenatal period, led by a trained midwife and psychology supporter, with each session lasting approximately 90 minutes. Sessions will be held at 3-week intervals, which is designed to maintain participant engagement but also allow participants enough time to try out practical strategies between sessions. As a further measure to support participants and maintain engagement, the midwife and psychologist delivering the groups will also send a weekly email to each participant to remind them to practise the skills from the previous group session and to ask whether they have any questions about the material. This can be stepped up to a telephone call if there is no response from a participant or if a telephone call is requested by the participant. Telephone calls will be limited to a maximum of 15 minutes in length, unless clinical imperative dictates otherwise.

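### The post-intervention assessment is fixed at 10 weeks from randomisation, so it follows the third group session only if a woman's group starts within 4 weeks, which nothing in the article secures

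*Protocol article*

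**What the plan says.** All references are to the protocol article.

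- **Recruitment procedure:** "Upon completion and receipt of the baseline measures, participants will be randomised". The trigger is the individual woman's own baseline return.
- **Randomisation:** "participants will be randomly allocated on a 1:1 basis to either the intervention group or the treatment as usual group", by sealed envelopes.
- **Sample size:** "30 participants will receive the intervention (in four groups of approximately 7–8 participants each", with partners where possible.
- **Study setting:** women are recruited through "antenatal scanning clinics at their 12-week scan in London and the South West of England", and the intervention is delivered in those same locations.
- **Intervention:** three antenatal group sessions are planned. "Sessions will be held at 3-week intervals".
- **Data collection:** the two assessments after baseline are set at "post intervention (10 weeks post randomisation), 8 weeks post intervention (18 weeks post randomisation".

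Three uses depend on the first of these assessments. Completion of the post-intervention measures is item 5 of the primary feasibility outcome. The quantitative analysis includes between-group pre-post effect sizes with confidence intervals on the GAD-7 and EPDS. The acceptability interviews are held at the post-intervention assessment. Under Aims and objectives, the information gathered, including the range of effect sizes, is to inform a fully powered trial.

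**The concern.** Two clocks run from different origins. The assessment clock starts for each woman at her own randomisation. The treatment clock starts when her group meets, and that cannot happen until enough women in her location have been allocated to the intervention. The label 'post intervention' ties the two together, but the article does not.

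A woman randomised early in the filling of a group uses up her 10 weeks while she waits. If she waits too long, her post-intervention GAD-7 and EPDS are taken before session 3, and her interview may ask about an intervention she has not finished. Session 3 is the only one of the three delivered entirely to women and partners together. The effect estimate carried forward to the full trial would then average over complete and partial treatment, in proportions set by recruitment speed, and would tend to be diluted. The count of completed post-intervention measures would be a count of week-10 measures under a label that does not fit every woman.

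**Working it through.** **1. The plan's own figures.** 10 + 8 = 18, so the two assessment labels agree with each other. Four groups of 7–8 give 28–32 women, which matches the planned 30. Neither figure is in error.

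**2. Slack before session 1.** Inputs: 3 sessions and a 3-week interval (Intervention); assessment at week 10 (Data collection). 'End of intervention' is taken as session 3; the self-led workbook and the informal postnatal session come later in any case.

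- Span from session 1 to session 3: (3 − 1) × 3 = 6 weeks.
- Longest wait that puts session 3 at or before week 10: 10 − 6 = 4 weeks.

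**3. What happens at other waits.** For a wait of w weeks, the sessions fall at weeks w, w + 3 and w + 6 from randomisation. The week-18 assessment falls 18 − (w + 6) = 12 − w weeks after session 3.

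| Wait for session 1 (weeks) | Session 3 at week | Sessions held by week 10 | Weeks from session 3 to the week-18 assessment |
|---|---|---|---|
| 0 | 6 | 3 | 12 |
| 2 | 8 | 3 | 10 |
| 4 | 10 | 3 | 8 |
| 5 | 11 | 2 | 7 |
| 7 | 13 | 2 | 5 |
| 8 | 14 | 1 | 4 |

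The week-10 label holds for waits up to 4 weeks. The label of 8 weeks post intervention is exact only at a wait of 4.

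**4. How often a wait over 4 weeks might occur.** The article gives no accrual rate, so this step is an illustration. Assumptions: each location randomises r women per week as a Poisson process; half go to the intervention; each location fills its own groups; a group of g women starts the moment its last member is allocated, with no set-up time.

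A woman who still needs k further intervention allocations waits more than 4 weeks if at most k − 1 such allocations occur in 4 weeks. Their expected number is 4 × r/2 = 2r. The share of the group waiting more than 4 weeks is therefore

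share = (1/g) × Σ P(Poisson(2r) ≤ k − 1), summed over k = 1 to g − 1.

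Worked case, r = 2 and g = 7: the Poisson(4) terms are 0.018, 0.092, 0.238, 0.433, 0.629 and 0.785. They sum to 2.195, and 2.195/7 = 0.31. For g = 8, add 0.889: 3.084/8 = 0.39.

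| Randomised per week per location | Group of 7 | Group of 8 |
|---|---|---|
| 1 | 57% | 63% |
| 2 | 31% | 39% |
| 3 | 14% | 20% |
| 4 | 5% | 8% |

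A simulation under the same assumptions gave the same figures.

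**5. The rate needed.** After the first woman, a group of 7–8 needs 6–7 more intervention allocations, which is 12–14 randomised women at 1:1. For the first woman to wait no more than 4 weeks on average, a location must randomise 12/4 = 3.0 to 14/4 = 3.5 women per week. Two locations at that rate would randomise all 60 women in about 60/7 = 8.6 to 60/6 = 10 weeks.

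**The case against.** The case on the other side has real force in several places.

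- **No outright contradiction.** A reader might infer that the schedule is impossible as written. It is not: it holds for any woman whose group starts within 4 weeks, and the 4 weeks may be a deliberate allowance for forming groups. This stands. What is missing is anything that keeps women within the allowance.
- **Batching may be in the full protocol.** Receipt of baseline is a precondition for randomisation, not a deadline, and holding women until dates are set would not breach the text. The flow diagram and the supplementary files are not available here. This is fair, but the point does not rest on an omitted detail. The article itself fixes the trigger for randomisation, the session spacing and the assessment anchor, and these agree only under a condition it does not state.
- **Session spacing is provisional.** The Intervention section leaves the final parameters to phase 1. That is true, but the anchor at 10 weeks is not described as provisional, and any change of spacing would change the slack.
- **The arms are not measured at different times.** A reader might infer a bias from differential timing. The text does not support that: both arms are assessed at the same interval from randomisation. The consequence is dilution and mislabelling. The count of sessions completed is also not tied to week 10, so it is not cut short by early assessment.
- **A group may start with fewer women.** The group size is only approximate, so a smaller group could begin sooner. This would lower the shares in the illustration.
- **A feasibility trial exists to find such things out.** In part, yes. But it can show whether groups fill in time only if waits and sessions held by each assessment are reported.

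**Conclusion.** The point holds as a conditional mismatch in timing. The 4-week limit and the 12 − w interval follow directly from the article's figures. They do not depend on whether groups are kept within one location, which is inferred from the Study setting section.

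The number of women affected cannot be derived from the document. The range of 5–8% to 57–63% rests on assumed accrual of 4 down to 1 randomised per week per location, Poisson arrivals, 1:1 allocation and full groups starting at once. It would be tempting to state that a third or a half of the intervention arm will be assessed too early; the article does not support any single figure. Recruitment began in November 2014 and was still ongoing in an article published in March 2016. That does not suggest that all 60 were randomised within 10 weeks, but the period may include phase 1 and publication delay, so no rate follows from it.

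For the women affected, the GAD-7 and EPDS effect sizes and the acceptability feedback would describe partly delivered treatment. That weakens an estimate meant to guide the full trial. The correction is worth making, although the analysis is descriptive and the comparison stays balanced in time.

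**What to change.** Reconcile the Recruitment procedure, Intervention and Data collection sections.

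1. Randomise in location-specific batches close to a scheduled group start: hold consented women with completed baselines until group dates are set, then allocate the batch 1:1.
2. Set the post-intervention assessment for both arms of a batch on the same date, just after that batch's third session, and the next assessment 8 weeks later. This keeps the arms aligned in time and makes both labels true.
3. Report, for each woman, the actual interval from randomisation to each assessment and, for intervention women, the number of sessions held by then.

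The cost is protocol wording and a change to the allocation list. The downside is a longer and unequal gap between baseline and randomisation, so that the pre measure is older for some women and some losses move to before randomisation, where they should still be counted in the flow of participants. Because recruitment had already begun, the first two changes could apply only to women not yet randomised; the third could apply to everyone.

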#### Clinical outcome measurements

A range of clinical outcome measures will be included in order to assess the feasibility and acceptability of these measures, and estimates of levels of symptoms in both trial arms at each assessment time point. Measures of the following will be included:Maternal anxiety, using the GAD-7 [38], a 7-item scale measuring symptoms of generalised anxiety disorder. The GAD-7 has excellent internal consistency (Cronbach’s *α* = .92) and good test-retest reliability (intraclass correlation = 0.83) [38]. When used in perinatal populations the GAD-7 has yielded a sensitivity of 61.3 % and specificity of 72.7 %, using a cut-off score of 13 [42]Maternal mood, using the Edinburgh Postnatal Depression Scale (EPDS) [43], a 10-item self-report scale used to assess antenatal and postnatal depression [43–45]. The EPDS has a high level of test-retest reliability (intraclass correlation = 0.92) [46]. In the second trimester of pregnancy the sensitivity of the EPDS is estimated to be 88 % and the specificity 91 %, when using a cut-off score of 9/10 [44]Pregnancy-specific worries, using the 10-item pregnancy-related anxiety scale [47]. The pregnancy-related anxiety scale has acceptable internal reliability (Cronbach’s *α* = .78) [47]Couple relationship, using the Dyadic Adjustment Scale (DAS) [48], a 32-item self-report measure of relationship adjustment. The DAS has been reported to have excellent internal consistency (Cronbach’s *α* = .915) [49]Birth outcomes, using an 8-item maternal self-report questionnaire, developed for this studyMother-child relationship, using the 25-item Postpartum Bonding Questionnaire (PBQ) [50]. The PBQ has been demonstrated to have acceptable internal consistency (Cronbach’s *α* = .76) [51]. For identification of any disorder of the mother-infant relationship the PBQ has yielded a specificity of 74 % and sensitivity of 84 % [52]Infant temperament, using a modified version of the Infant Behaviour Questionnaire (IBQ) [53]. Each subscale of the IBQ has been reported to have acceptable or good internal reliability: activity level (*α* = .73), smiling and laughter (*α* = .85), fear (*α* = .80), distress to limitations (*α* = .84), soothability (*α* = .84), and duration of orienting (*α* = .72) [53]Infant sleep, using the Brief Infant Sleep Questionnaire [54]. This questionnaire has good test-retest reliability; significant correlations are reported between the repeated sleep measures for daytime sleep duration (*r* = .89), settling time (*r* = .94), nocturnal sleep-onset time (*r* = .95), nocturnal sleep duration (*r* = .82), number of night wakings (*r* = .88), and duration of nocturnal wakefulness (*r* = .95) [54]Health-related quality of life of the mother, using the EuroQol-5D-3 L measure [55] recommended by National Institute for Health and Care Excellence (NICE) for inclusion in economic evaluations Health economics: the economic component of the proposed work will involve use of the Adult Service Use Schedule (AD-SUS) [56], a questionnaire designed for application to mental health populations, including depression and anxiety

### Data analysis

#### Quantitative data analysis

Data analysis will be primarily descriptive to aid the planning of a future RCT. Participant flow through the study will be presented following CONSORT guidelines [36]. Descriptive data will be presented in the form of means and standard deviations; medians and ranges; or percentages with 95 % confidence intervals, as appropriate depending on the data being described. The following will be calculated: (1) percentage of participants meeting eligibility criteria, (2) percentage of individuals consenting to the study, (3) percentage entering the randomisation phase, (4) the number of sessions completed by those in the treatment arm, (5) percentage completing the outcome measures at post-treatment follow-up, (6) between group pre-post effect sizes and confidence intervals on the GAD-7 and EPDS.

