The three group sessions are designed to address specific antenatal anxieties, and will support participants in developing key practical skills. A group mode of delivery has strong potential to be more cost-effective and sustainable and less time-consuming for midwives than individual support, and will also enable mutual support and interaction between group members, thereby fitting well with the existing models of antenatal care. Furthermore, it could be easily integrated into current routine NHS antenatal services and would, therefore, be widely available and accessible to a broad range of pregnant women. The specific parameters of the intervention and its delivery will be finalised in light of the pilot work undertaken in phase 1 of the research programme, but the aim is to base the three group sessions on a number of key themes, including psychoeducation on anxiety during pregnancy, problem-solving, communication and other strategies and techniques to help with managing anxiety and stress including self-care and compassion (Fig. 2).

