### Control: treatment as usual

Women randomised to the control group will continue to receive their usual care for antenatal anxiety. Although there is currently no standard model of care for antenatal anxiety, this may include care provided by their general practitioner (GP), midwife, health visitor, local Improving Access to Psychological Therapies (IAPT) service or community mental health team. The care received by women in the trial will be actively monitored by the research group, using the Adult Service Use Scale (AD-SUS).

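### Only the intervention arm is treated in four therapy groups, yet the planned GAD-7 and EPDS effect-size intervals include no stated allowance for group

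*Protocol article*

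**What the plan says.** Allocation is individual: "participants will be randomly allocated on a 1:1 basis" (Randomisation). The Sample size section takes 30 per arm from guidance on pilot trials, reports that "no formal power calculation has been conducted", and places the 30 intervention women "in four groups of approximately 7–8 participants each, plus participants’ partners where possible". The Intervention section has each session led by a midwife and a psychology supporter, and gives as one reason for the group format that it "will also enable mutual support and interaction between group members". The comparator has no groups: "Women randomised to the control group will continue to receive their usual care for antenatal anxiety" (Control: treatment as usual).

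The Quantitative data analysis section describes the analysis as mainly descriptive and gives a numbered list of what will be calculated. Item (6) is "between group pre-post effect sizes and confidence intervals on the GAD-7 and EPDS". No model, variance formula or degrees of freedom is given. Therapy group is not mentioned in the list, and no within-group correlation is among the quantities. Both the Aims and objectives and the Sample size sections say that the results will help to design and size a definitive trial.

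**The concern.** This is a partially nested design: randomisation is individual, but after allocation one arm is clustered and the other is not. Women in the same group share sessions and leaders, and the protocol intends them to influence one another, so their outcomes may be correlated. An ordinary two-arm interval ignores that correlation and understates the variance of the intervention-arm mean.

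Two things are at stake. The GAD-7 and EPDS intervals could look more precise than they are. And a definitive trial of the same group intervention, if sized with no design effect, would recruit too few women. Planning that trial is a declared purpose of the pilot.

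**Working it through.** The plan has no power calculation to reproduce. Its group arithmetic is consistent: 4 × 7 = 28 and 4 × 8 = 32 bracket 30, and 30/4 = 7.5.

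**Inputs**
- From the article: 30 per arm; four groups in the intervention arm, mean size m = 7.5; no groups in the control arm; d = 0.58 for anxiety in the earlier trial of the workbook intervention (Intervention section).
- Assumed: the ICC, since the article gives none (range 0 to 0.20); a 95% level for the effect sizes, since the article states it only for percentages; equal total variance in the two arms.

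**Formulae** (in SD units)
- Design effect in the intervention arm: DE = 1 + (m − 1) × ICC = 1 + 6.5 × ICC.
- Ordinary SE: √(2/30) = 0.258; 95% half-width 1.96 × 0.258 = 0.506.
- SE allowing for groups: √(DE/30 + 1/30).
- SE ratio r = √((1 + DE)/2).
- Coverage of the ordinary interval: 2Φ(1.96/r) − 1.

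| ICC | DE | r | Half-width | Coverage of ordinary 95% interval |
|---|---|---|---|---|
| 0 | 1.000 | 1.000 | 0.506 | 95.0% |
| 0.01 | 1.065 | 1.016 | 0.514 | 94.6% |
| 0.05 | 1.325 | 1.078 | 0.546 | 93.1% |
| 0.10 | 1.650 | 1.151 | 0.583 | 91.1% |
| 0.20 | 2.300 | 1.285 | 0.650 | 87.3% |

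**Small-sample degrees of freedom.** With four groups, the intervention-arm variance has 3 degrees of freedom and the control arm 29. At ICC 0.05 the Satterthwaite value is about 8.7 and the half-width is 0.633. An ordinary t interval on 58 degrees of freedom has half-width 0.517, and 0.633/0.517 = 1.22. Part of this comes from the degrees of freedom alone: at ICC 0 the corresponding half-width is 0.569, and 0.569/0.517 = 1.10.

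**Can the pilot supply the ICC?** In 20,000 simulated trials with groups of 8, 8, 7 and 7 and a true ICC of 0.05, the central 95% of ANOVA estimates ran from about −0.14 to 0.36, and 45% were zero or below.

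**Illustrative definitive trial** (d = 0.58, 80% power, two-sided 5%, equal arms, m = 7.5). Under independence: 2 × (1.96 + 0.84)²/0.58², rounded up to 47 per arm. Multiplying 47 by (1 + DE)/2:
- ICC 0.05: 47 × 1.1625 = 54.6, so 55 per arm.
- ICC 0.10: 47 × 1.325 = 62.3, so 63 per arm.

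**The case against.** The strongest objection is that the article names a quantity and not a method. A reader might infer that the plan treats all 60 women as independent. It does not say so; that reading rests on silence, and the full protocol or analysis plan, neither of which is shown, may handle therapy group. This stands, and it makes the finding about interval width conditional. What remains is that the numbered list sits beside a stated group design and a stated sample-sizing purpose and makes no allowance for group.

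A reader might extend the point to the percentages and their 95% intervals. The list does not support that. Items (1) to (3) arise before any woman joins a group, item (4) is a number of sessions, and item (5) is not stated by arm.

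A reader might also conclude that the pilot should deliver the ICC for the definitive trial. The simulation shows that four groups cannot do this to any useful precision.

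The harm to the later trial is likewise conditional. Nothing says it would be sized without a design effect, and the pilot SD is hardly disturbed by clustering: at ICC 0.05 the expected intervention-arm sample variance falls by about 6.5 × 0.05/29, or 1%. The shortfall would come from omitting the design effect at the planning stage.

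Finally, the primary outcome is feasibility of recruitment and data collection (Feasibility and acceptability), and the article bases no hypothesis test or progression rule on these intervals. This limits the severity.

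**Conclusion.** The point holds in conditional form. The design is clustered in one arm, the plan names the mechanism for correlation, and the listed GAD-7 and EPDS intervals carry no stated allowance for it. If they are computed as ordinary two-arm intervals, the correct SE is about 2% larger at ICC 0.01, 8% at 0.05 and 15% at 0.10, with true coverage of about 93% at 0.05 and 91% at 0.10. At ICC 0 there is no understatement of the SE. For a definitive trial at d = 0.58 and 80% power, leaving out the design effect means 47 per arm where 55 (ICC 0.05) or 63 (ICC 0.10) would be needed.

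These sizes rest on an assumed ICC, a mean group size of 7.5 and equal total variance in the arms. This is a should-fix and not a must-fix, because the estimates are secondary and descriptive.

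**What to change.** In item (6) of Quantitative data analysis, state that the GAD-7 and EPDS effect-size intervals allow for therapy group in the intervention arm only, with each control treated as a group of one. Report them under a fixed range of ICCs, for example 0, 0.05 and 0.10. Give the definitive trial's sample size over the same range, and do not rely on an ICC estimated from the pilot's four groups.

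The cost is a change of analysis wording plus a record of which group each intervention woman belonged to; no new outcome data are needed. The intervals become about 8% to 15% wider at ICCs of 0.05 to 0.10, or about 22% wider at ICC 0.05 if small-sample degrees of freedom are also used.
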